# Sing4Health: protocol of a randomized controlled trial of the effects of a singing group intervention on the well-being, cognitive function and health of older adults

**DOI:** 10.1186/s12877-020-01686-6

**Published:** 2020-09-18

**Keywords:** Singing groups, Intervention, Randomized controlled trial, RCT, Cognitive function, Health indicators, Well-being, Older adults, Mediation analyses

## Abstract

**Background:**

Singing is a multimodal activity that requires physical, cognitive and psychosocial performance, with benefits to various domains of well-being and health in older adults. In recent years, research has increasingly studied group singing as an important cost-effective intervention to promote active and healthy aging. However, the specific factors responsible for these benefits need further experimental support, as most studies do not allow for causal inferences. This study responds to the need for further randomized controlled trials (RCT), with follow-up measurement, on the benefits of group singing in older adults from a low socioeconomic background. Also, while most studies often focus on specific outcome measure dimensions, in this study, the conjoint effect of several physical, psychosocial, psychoemotional and cognitive dimensions are analyzed, testing mediation effects of psychosocial and psychoemotional variables on the well-being and health of the participants.

**Methods:**

We implement and measure the effects of a singing group program for older adults, with an RCT crossover design study, in a natural context, before and after the intervention and in a follow-up, 6 months after the intervention.

**Participants:**

140 retired older adults (> 60 years) users of a social support institution, will be invited to participate in a singing group program and randomly allocated to an experimental (*n* = 70) and a control (*n* = 70) group, which will enroll in the regular activities proposed by the institution. The intervention consists of 34 bi-weekly group singing sessions, of 2 h each, for 4 months. Measures on social and emotional well-being, cognitive function, and health indicators (e.g., blood pressure, glycemia, cholesterol, c-reactive protein, sedimentation rate, respiratory function, body balance, sleep quality, medication intake, and health services attendance) will be collected. Interviews will be conducted on the motivation and perceived benefits of participation.

**Discussion:**

Significant improvements are expected in the outcome measures in the experimental group after the intervention, validating singing groups as a cost-effective intervention for healthy aging. Psychosocial and psychoemotional variables are expected to be mediators of the effects of the program in the cognitive function, well-being and health of the participants.

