**Trial registration:**

NCT03985917. Registered 14th June 2019 (retrospectively registered).

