#### Perceived benefits of singing

In qualitative studies on the perceptions of older adults’ participation in singing groups, social support and increased interaction between participants, the expression of positive emotions and knowledge acquisition are reported [13], as well as the emotional, physical and mental well-being and learning new things [45]. In this study, interviews will be collected on the perceived motivations, expectations and benefits of those participating in the program, allowing to substantiate the quantitative and qualitative results of the study and thus achieving a higher understanding of the results.

As previously stated, the scientific literature on singing group interventions has demonstrated benefits on the well-being, quality of life, lung function, depression, anxiety, and stress symptoms of older adult participants [28]. However, literature reviews also highlight the lack of RCTs with blinding of conditions and follow-up collection, and limitations of the studies including biased selection of participants, small sample sizes, and selective reporting of outcomes, resulting in the weak validity of some of the results. More RCTs are needed to further validate the benefits of singing groups on the emotional and social well-being, cognitive function and health of the participants (Clark & ​​Harding, 2012; Clift et al., 2016; Dingle et al., 2019) [28, 46, 47].

In this study we aim to overcome some of the gaps in the literature, implementing a pragmatic RCT study, with a 6 months’ follow-up and single-blinded data collection. The protocol of the study was pre-registered to avoid selective outcome reporting. The study enrolls a sample of 140 participants, including young and old older adults from disadvantaged socioeconomic groups, not previously involved in singing groups. This is also a mixed method study with quantitative and qualitative data analysis. The study tests the causal effects of a singing group program on the psycho-emotional, psychosocial, cognitive, and health biomarkers variables, assessed through a series of self-reports, physical trace records, and cognitive and physical performance tests. The study will also qualitatively analyze the participants’ perceptions of their motivations and of the benefits of participating in the program, allowing us to establish relationships with the quantitative results obtained through the RCT design of the study.

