Our hypotheses are that participating in group singing will significantly improve the emotional and social well-being, cognitive function, and the general health of the participants after the program, and significantly different to the control group. We also hypothesize that psychoemotional variables (e.g. self-esteem; depression, anxiety and stress), and psychosocial variables (e.g. social identification; loneliness), will mediate the effects of the singing group program on cognitive function (e.g. executive function, verbal memory), well-being and health (e.g. blood biomarkers, respiratory and motor functions) of the participants (see Fig. 1).

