### Materials

The study aims to measure a set of biopsychosocial variables, described below, divided into four domains: psychoemotional, psychosocial, cognitive and health. All measures will be collected to measure change from baseline at 4 months (post-test) and at 10 months (follow-up).

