#### Psychoemotional variables

**Life Satisfaction** will be measured by the Satisfaction with Life Scale (SWLS, Diener, Emmons, Larsen, & Griffin, 1985) validated to the Portuguese by Neto, Barros, and Barros (1990) [48, 49]. Satisfaction with life in general is assessed according to the person’s own criteria. Consists of five items, answered on a 5-point scale from: 1 ‘strongly disagree’; to 5 ‘I agree very much’.

**Positive and Negative Affect** will be measured by the PANAS - Positive and Negative Affect Schedule (Watson, Clark, & Tellegen, 1988) validated for the Portuguese by Galinha and Pais-Ribeiro (2005) [50, 51]. It consists of two scales with 10 items each, which measure the frequency of positive emotions and negative emotions (e. g, “To what extent did you feel each of the following emotions during the last days”: enthusiasm, distress, etc.) on a five points Likert scale (from 1 “nothing or very slightly”; to 5 “extremely”).

**Self-Esteem** will be measured by the Rosenberg Self-Esteem Scale (RSES, Rosenberg, 1965) validated for the Portuguese by Pechorro, Marôco, Poiares, and Vieira (2011) [52, 53]. Assesses the appreciation of self-worth and self-acceptance, with 10 items, answered on a 4-point Likert scale, from 1 ‘strongly disagree’ to 4 ‘strongly agree’.

**Depression, Anxiety and Stress** will be measured by the DASS-21 (Lovibond & Lovibond, 1995) validated for the Portuguese by Pais-Ribeiro, Honrado and Leal (2004), which consists of 21 items distributed over 3 subscales of 7 items each, related to one of the following constructs: depression, anxiety or stress [54, 55]. The response to the items, the extent to which the each sentence applies to the subject in the last 4 months is classified using a Likert 4-point scale ranging, in terms of severity or frequency, from 0 “It did not apply to me” to 3 “Applied to me most of the time”.

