#### Psychosocial variables

**Quality of Life** dimensions will be measured by two instruments:
The **World Health Organization Quality of Life – Old** (WHOQOL-OLD) from Power, Quinn, Schmidt, & The WHOQOL-OLD Group, 2005), adapted to the Portuguese by Vilar (2015) [56, 57]. The WHOQOL-OLD measures the quality of life specifically for older adults, with 28 items, measuring six dimensions. In this study the dimensions (1) sensory abilities; (2) autonomy; and (4) social participation will be measured. The items are answered in a 5-point scale, from 1 (Nothing; Very Bad; Very Unsatisfied) to 5 (Extremely; Very Good; Very Satisfied);The **World Health Organization Quality of Life – Bref** (WHOQOL-BREF, WHOQOL Group, 1998) adapted to the Portuguese by Vaz Serra et al. (2006) [58, 59]. The WHOQOL-BREF measures the subjective perception of quality of life. It consists of 26 items, of which two items measure global quality of life and 24 items measure four dimensions. In this study the (1) Physical health, (2) Psychological Health, and (3) Social relationships will be measured. The items are answered in a 5-point scale, from 1 (Very Bad; Very Unsatisfied; Nothing; Never) to 5 (Very Good; Very Satisfied; Extremely; Always).

**Loneliness** will be measured by the UCLA Loneliness Scale (Pocinho, Farate, & Dias, 2010) [60]. Assesses the feeling of being cut off from others, with four items, derived from the longer version of the ULS-20, answered on a 4-point scale from: 0 ‘Never’, to 4 ‘Often / Many Times’.

**Social Identification** will be measured by the Four Item Measure of Social Identification FISI (Doosje, Spears, & Ellemers, 1995) [61]. Assesses the emotional evaluation of the relationship between the self and the ingroup, with four items answered on a Likert scale, ranging from 1 ‘strongly disagree’ to 7 ‘strongly agree’.

**Social Well-Being** will be measured by the Scale of Social Well-Being (Keyes, 1998) adapted for the Portuguese by Silva (2016) [62, 63]. Assesses a multidimensional construct encompassing the dimensions: social acceptance, social coherence, social actualization, social integration and social contribution. In this study we will use a short version of 6 of the 33 items, answered on a Likert scale ranging from 1 ‘strongly disagree’ to 6 ‘strongly agree’.

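### About 40 outcome scores have equal status with none named primary, and the safeguard cited against selective reporting conflicts with the article's own registration entry

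*Protocol article*

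**What the plan says.** The Materials section describes the variables as "divided into four domains: psychoemotional, psychosocial, cognitive and health" and treats them alike: "All measures will be collected to measure change from baseline at 4 months (post-test) and at 10 months (follow-up". The sections that follow list the instruments, several of which give more than one score. The DASS-21, for example, is one "which consists of 21 items distributed over 3 subscales of 7 items each", and for the WHOQOL-BREF: "In this study the (1) Physical health, (2) Psychological Health, and (3) Social relationships will be measured".

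The hypothesis at the end of the Background covers every domain: "participating in group singing will significantly improve the emotional and social well-being, cognitive function, and the general health of the participants". The statistical paragraph (at the end of the section on perceived motivation, expectations and benefits) applies mean comparisons to the outcome measures across three time points and between groups. It sets no order among them and gives no significance level. The Participants section gives 88% power for an eta-squared of 0.14 with 70 per group, and 79% after 15 dropouts per group, without saying which outcome or test is meant.

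The abstract's Discussion states what is to be concluded: "Significant improvements are expected in the outcome measures in the experimental group after the intervention, validating singing groups as a cost-effective intervention".

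On safeguards, the section on perceived benefits of singing names selective outcome reporting as a weakness of earlier studies and then says: "The protocol of the study was pre-registered to avoid selective outcome reporting". The Trial registration entry reads: "Registered 14th June 2019 (retrospectively registered)".

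**The concern.** With about 40 scores of equal rank, a reader of the results cannot tell which one the trial was designed to answer. If each is tested in the usual way, some are likely to reach significance by chance, and the article gives no basis for separating those from a planned main result. The power statement does not help, because it points to no outcome.

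A registration dated before the trial would have limited the freedom to choose a headline afterwards, and the article relies on this. Its registration entry says otherwise. What is at stake is the trial's central claim, that the programme is validated for older adults, which could come to rest on whichever scores happened to move.

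**Working it through.** **1. The plan's own figure.** Eta-squared 0.14 gives f = √(0.14/0.86) = 0.403 and, for two equal groups, d = 2f = 0.807. A two-group F test at two-sided 0.05 (assumed) then has 99.7% power at 70 per group and 98.7% at 55 per group. The stated 88% and 79% are not reproduced. They correspond to an eta-squared of about 0.066 (d about 0.53). Unstated settings also come within 2 points, such as a repeated-measures between-groups test with f = 0.25 and correlation 0.7 (89.0% and 80.5%), or a MANOVA on 8 responses with f² = 0.14 (88.9% and 77.5%). The mismatch is a separate problem. For this point it shows that the powered test cannot be identified from the article.

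**2. Counting the scores** (from the four variable sections):

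| Domain | Scores | Number |
|---|---|---|
| Psychoemotional | SWLS 1, PANAS 2, RSES 1, DASS-21 3 | 7 |
| Psychosocial | WHOQOL-OLD 3, WHOQOL-BREF 3, loneliness 1, social identification 1, social well-being 1 | 9 |
| Cognitive | MoCA 1, RAVLT 1, TMT-A 2, Digit Symbol 1 | 5 |
| Health: biomarkers and spirometry | blood pressure 1–2, pulse, weight, glycemia, cholesterol, CRP, ESR, six spirometry measures | 13–14 |
| Health: other | balance, physical activity, sleep, pain 1–2, service attendance, medication | 6–7 |

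The total is 40 to 42, and 41 is used below. The count leaves out the six separate MoCA functions, the 10-month comparisons, the sub-group analyses and the mediation models.

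**3. False positives with no true effect**, each score tested once at two-sided 0.05:

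- Expected number: 41 × 0.05 = 2.05, whatever the correlation. In favour of singing: 41 × 0.025 = 1.03.
- At least one, independent outcomes: 1 − 0.95^41 = 87.8% (87.1% for 40 scores, 88.4% for 42).
- At least one in favour of singing, independent: 1 − 0.975^41 = 64.6%.

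**4. Allowing for correlation.** The outcomes are certainly correlated, but the article gives no correlations. The simulation drew 41 equally correlated standard normal statistics, z_j = √ρ·c + √(1−ρ)·e_j, 200,000 times. A false positive is |z_j| > 1.96, or z_j > 1.96 for results favouring singing.

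| Common correlation | At least one, either direction | At least one favouring singing |
|---|---|---|
| 0 (exact) | 88% | 65% |
| 0.1 | 86% | 55% |
| 0.3 | 75% | 41% |
| 0.5 | 58% | 29% |
| 0.7 | 38% | 19% |

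Naming one outcome per domain without adjustment would still give 1 − 0.95^4 = 18.5% if independent, so four primaries need a correction.

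**5. The two registration statements.** One says registration came beforehand and was meant to prevent selective reporting. The other gives 14 June 2019 and calls it retrospective. Both cannot be right, and no analysis plan, seen or unseen, can reconcile them.

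**The case against.** The strongest reply is that this is a condensed article. A multiplicity method normally belongs in a statistical analysis plan, which is not shown, and the registry may name a primary outcome. A reader might infer that the trial has no error control at all, but the article does not establish that. What stands is narrower. The article describes every instrument, states power and states hypotheses, yet does not say which outcome is the main one. That is design content, and the power statement has no clear meaning without it.

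A reader might also infer that a single significant score would be declared a success. The abstract sentence is an expectation and not a success rule, and the hypothesis joins the domains with *and*, so read literally one chance result would not confirm it. The article nevertheless does not say how many results, or which, would.

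It is tempting to quote 88% as the risk. That is the ceiling: it assumes independence and counts results against singing as well. The figures for favourable results are lower, and 19% at correlation 0.7 is not very likely in any ordinary sense. All of them remain well above the 2.5% that one two-sided test would allow in that direction.

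Lastly, retrospective registration does not show that protection is absent. The article gives no enrolment or data-collection dates to set against June 2019, so registration may still have come before the outcome data or their analysis. The safeguard is weaker than claimed; how much weaker cannot be told from the document.

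**Conclusion.** The point holds in this form: the article gives about 40 scores equal status, names no primary outcome, ties its power to none of them, and contradicts itself on the registration it cites as protection. With no true effect, about two false positives are expected from 41 tests, one of them in favour of singing. The chance of at least one lies between about 38% and 88% in either direction, and between about 19% and 65% in favour of singing, for common correlations from 0.7 down to 0. Chance results could therefore be read as validating the programme.

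These figures assume two-sided 0.05 per score (not stated in the article), one test per score, no adjustment set out elsewhere, and equal correlation. The further tests left out of the count would raise them. The registration contradiction depends on none of these assumptions.

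**What to change.** - Name one primary outcome at T1, the end of the phase that the Study design section describes as randomised. Alternatively name one per domain (four), tested by Holm at an overall 0.05. If the registry already names a primary outcome, state that one.
- Label all other outcomes secondary, with false-discovery-rate control or as estimates with intervals.
- Tie the power statement to the primary outcome or outcomes and name the test.
- In the section on perceived benefits of singing, change the claim of pre-registration to retrospective registration.
- Date and post the hierarchy before arm-level data are analysed. Some passages, including the account of the invited singers and of the two intervention groups, are already in the past tense. If arm-level data have been seen, say that the hierarchy is post hoc.

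**Cost.** No extra participants or measurements are needed. A single primary outcome costs no power. With four, Holm's first step uses 0.05/4 = 0.0125. The detectable difference at 80% power is (z for alpha + 0.842) × √(2/n):

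- 70 per arm, alpha 0.05: (1.960 + 0.842) × √(2/70) = 0.47, or 0.48 with the t distribution.
- 70 per arm, alpha 0.0125: (2.498 + 0.842) × √(2/70) = 0.56, or 0.57 with the t distribution.
- 55 per arm, alpha 0.0125: (2.498 + 0.842) × √(2/55) = 0.64, or 0.65 with the t distribution.

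All are below the 0.81 that the article's own eta-squared of 0.14 implies. If the arm-level results are already known, rewording cannot restore a prespecified hierarchy; disclosure is then what remains.

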**Trial registration:**

NCT03985917. Registered 14th June 2019 (retrospectively registered).

## Background

Current demographic trends require validating and implementing cost-effective intervention community programs to promote physical activity, cognitive functioning, social participation, and well-being among older adults [1–3], particularly those from socioeconomically disadvantaged groups [4].

Group singing is a culturally universal activity, with potential health benefits for seniors [5]. It involves a combination of cognitive, psychosocial and physical components associated with multiple health and well-being improvements [6–8], constituting a cost-effective intervention strategy [6]. However, it is not clear what factors are responsible for these benefits, nor whether they can be causally attributed to the singing or biased self-selection of the participants. There is a lack of experimental studies capable of answering these questions [4, 9]. There is a need to expand the body of research to clarify the feasibility and effectiveness of group singing on a range of older adult physical and cognitive health outcomes [10].

### Psychoemotional aspects

Group singing has been shown to have an important impact on psychoemotional variables, stimulating emotional expression, pleasure, fun, relaxation and imagination [11]. It also fosters a sense of meaning to life, self-awareness and self-esteem [12]. In a randomized controlled trial (RCT) study with healthy older adults (*N* = 258), Coulton et al. (2015) analyzed the effects of participating in a community singing group for 3 months and a follow-up 6 months after randomization and found that participating had positive short and long-term effects on mental health, in terms of quality of life, anxiety and depression [6]. In a second RCT study with older adults from day care centers (*N* = 26), Pires, Galinha, and Herédia (2017) found that a one-month short program of group singing significantly reduced negative affect after the intervention. The positive effects, however, did not sustain until the follow-up, 8 weeks after the intervention [13]. Both RCT studies included mixed methods and the qualitative data corroborated the quantitative results. Participants reported benefits in emotional well-being along with social and physical benefits [6, 13, 14]. Mohammadi, Tanaze and Moradi (2011) in a third RCT study, with a music therapy intervention for elderly in the community (*N* = 19), that also included a group singing component, also observed a significant decrease in anxiety, stress and depression levels [15].

Other non-experimental studies also found associations between group singing and psychoemotional variables. For example, in a longitudinal study that included 633 individuals who participated in choir singing groups, the quality of life was improved, but it was difficult to recognize the direct effects of singing on the well-being [12]. Two cross-sectional studies of choir singing, were able to find a significant relation between the perceived benefits of choir singing and better quality of life on the psychological, social relations and environmental domain dimensions [16] and a better quality of life in terms of their physical health than a comparison group - even when involved in other hobbies - the singing group participants reported significantly higher overall quality of life [17]. Both singing and music listening were able to change the mood of participants immediately after a short (half an hour) session and some of the effects were visible in mood levels a week later. Although the effects were more robust for the singing group, no significant differences were found in comparison with the music listening group [18].

The present study contributes with new results on the causal effects of singing groups with old older adults from low socioeconomic backgrounds. Psychoemotional benefits on positive and negative affect, anxiety, depression and stress, self-esteem, global life satisfaction and quality of life with psychological health will be tested. Importantly, controlled causal effects of singing on some of these variables were not found in the literature. The study also allows for a conjoint analysis of benefits to the psychoemotional domain related with the other social, cognitive, and biological domains. Finally, the study is innovative in analyzing mediation effects of the psychoemotional and psychosocial variables in the effects of group singing on other domains, such as cognitive and biological health variables.

